### Recruitment

To assure adequate recruitment to the trial, the study will take place at three departments simultaneously. Recruitment from three departments should provide sufficient participants to ensure the target sample size. In case of insufficient recruitment further recruiting centers will be sought and included if possible.

### Assignment of interventions

The randomization process will be handled by the regional pharmacy in Region Zealand, Denmark. The randomization list/sequence will be made before the study start by using a dedicated online software (http://www.randomization.com/) by the regional pharmacy. Block randomization, in blocks of 6, will be used. In each block, half the patients will receive the intervention drug (melatonin 25 mg), and the other half the placebo. The randomization list will be kept at the regional pharmacy and will not be available to the investigators recruiting the participants.

Allocation concealment consists of two sets of coded envelopes (an opaque, sealed envelope for each patient, containing the randomization code for each patient) which will be produced by the Regional Pharmacy of Region Zealand. The two envelopes will be sent to Koege Hospital (sponsor’s center) and stored there; one in the patients Case Report Form (CRF), and the other in the Trial Master File (TMF). In this way, the blinding will be conserved for both the sponsor/investigator and other investigators who enroll and assign treatments to the participants.

After assignment into the trial, the trial participant, investigators, care providers, outcome assessors and data analysts will be blinded to the allocated treatment. In case of a suspected unexpected serious adverse reaction (SUSAR), unblinding can be performed by the investigators using the coded envelopes available in the patient’s CRF.

### Data collection

Data are collected in participant-specific Case Report Forms (CRFs) and will be stored for a 5-year period after study termination. As standard, an electronic CRF (eCRF) will be used to collect all study data from each participant throughout the study. The eCRF is created using the online platform Easytrial.net (Easytrial ApS, Glostrup, Denmark) which serves as the electronic data storage of the clinical trial. The individual questionnaires are sent to the individual participants via email with a unique generated link. In case a participant is noncompliant with the electronic setup (i.e., no Internet connection), they will fill out study questionnaires in paper format and the data will be transferred manually to the online study database. At the point of inclusion, baseline demographics will be collected from the patient and the patient record.

As previously described, phone calls and electronic (e.g., email) reminders will be sent out to assure participant retention and reduce loss to follow-up. No additional data are to be collected if a participant discontinues study medication or in other ways does not comply with the intervention protocols.

Using the eCRF implies that answered questionnaires are source data and are transferred directly to the electronic database upon completion. The sleep diary and the VAS administered for the initial 2 weeks are in paper format, and will later be transferred to the electronic database using double data entry. The study will be performed in accordance with Good Clinical Practice (GCP) and monitored by the GCP Unit from the University of Copenhagen. After completion of the trial the sponsor/investigator (first author) will have access to the final trial dataset.

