### Interventions

Patients will receive either 25 mg exogenous melatonin (intervention group) or matching placebo (control group) in an orally administered pill. Regarding the active substance each pill will contain 12.5 mg melatonin, and the placebo pill will be comparable to study medication except for the active substance. The medication will be packaged in blister packs consisting of 30 pills in each, and a total of seven blister packages will be packaged in a cardboard box (total of 210 pills). Patients will be instructed to take two pills (daily dose of 25 mg active substance) approximately 1 h before bedtime during the entire length of the study (12 weeks). Medicine compliance will be investigated at weeks 2 and 12 at clinical visits. All study medication will be produced by PharmaNord Aps. (Vejle, Denmark) in accordance with Good Manufacturing Procedure (GMP). The study medication will be shipped to the Region Zealand Hospital Pharmacy which will handle the randomization process.

If a participant withdraws their consent, they will leave the study. In the unlikely event that a female participant should become pregnant despite using reliable birth control, she will leave the study. Patients who have a recurrence of ACS during the study will be withdrawn from the study. In case of severe medical emergency (e.g., stroke or severe sepsis) requiring emergency surgery, stay in an intensive care unit, or more than 1 week of hospitalization will result in exclusion from the study. Diagnosis of a cancer during the study period will also result in withdrawal from the study. No further data will be collected from patients after leaving. However, previously collected data will be part of the final data analysis. No change in dose of study medication will be possible during the trial.

A medicine compliance of a minimum of 75% (pill count) at the clinical visits at weeks 2 and 12 are required. If the patients do not comply with these demands at either visit, they will be excluded from the study. Exclusion from the study entails stopping the study medication, and patient’s data will not be part of a per-protocol analysis. In case of medicine compliance at the first clinical visit, the data collected until this point will be part of a per-protocol analysis.

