If a patient is diagnosed with a moderate-to-severe depression on the MDI during the study, they will be referred to a psychiatrist in training attached to the study (who is blinded to the allocated treatment). The psychiatrist in training will perform a structured clinical interview (Hamilton Depression Scale) with the purpose of diagnosing depression and its severity according to the *International Classification of Diseases, version 10* (ICD-10) criteria. Patients with a moderate-or-severe depressive episode according to the Hamilton Depression Scale and clinical assessment will be withdrawn from the study and offered open treatment for depression via the patient’s general practitioner (GP). All outcome data collected until the eventual termination in the study will be part of the final analysis. If the patient is diagnosed with a mild depression on the MDI, they will be allowed to continue in the study. The patient will be monitored using the MDI and phone calls according to the study protocol. In case of symptom progression on the MDI into moderate to severe depression, the participant will be referred to the psychiatrist in training as described above.

Patients will be contacted by phone seven times (every 2 weeks) during the trial to assure compliance and to promote their retention during follow-up. The patients will be reminded to fill in the relevant study questionnaires, reminded to take study medication, and monitored for occurrence of any adverse reactions, or changes in other medication since last contact with study investigators.

The participants are allowed to participate in all offered concomitant care at their regional cardiology department (e.g., cardiac rehabilitation). Startup of any medical antidepressant treatment in the trial period is prohibited and will lead to exclusion from the trial.

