### Statistics

Descriptive data on baseline characteristics and results will be presented as mean, SD, and *n* and presented in tabular form. Distribution of data will be tested by using data plots and by visually assessing data, and potentially continuous variables will be visualized in a matrix plot. Appropriate statistical tests will be used accordingly depending on distribution. Log transformation will be applied if applicable.

Our null hypothesis is that there will be no difference in the number of participants developing depressive symptoms (defined as a MDI score ≥21) throughout the study period between the melatonin and the placebo group. The hypothesis is assessed using Fisher’s exact test and/or the chi-squared test.

For the primary outcome analysis, a linear mixed model will be applied. The effect of age, gender, comorbidity and cardiac risk factors will be assessed by marginal analysis. Results will be assessed through an analysis on complete data generated using multiple imputation.

As a secondary analysis, the cumulative incidence of depressive symptoms will be plotted for the two groups and compared using the log-rank test assuming the absence of competing risks. Incidence of depressive symptoms (MDI score ≥21) will be analyzed using the Cox proportional hazards regression, including analysis of effects of age, gender, comorbidity and cardiac risk factors at baseline.

A principle analysis will be performed according to the intention-to-treat principle (ITT). The intention-to-treat population is defined as every patient randomized into the trial. A per-protocol analysis will also be performed. A per-protocol participant is defined as a patient who has taken medication in accordance with the protocol (at least 75%) for the first 14 days (until the follow-up visit). In cases of noncompliance with the medication before the follow-up visit (i.e., exclusion from the study), another patient will be enrolled to make up for the lost patient. Finally, a standard sensitivity analysis will be performed on the per-protocol patient population.

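### No MDI is collected after a patient stops medication or leaves, so the intention-to-treat result rests on an assumption about off-treatment outcomes that the trial's data cannot check

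*Protocol article*

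**What the plan says.** The Statistics section of the protocol article makes the intention-to-treat analysis the principal one and sets its population: "The intention-to-treat population is defined as every patient randomized into the trial". On missing data it says: "Results will be assessed through an analysis on complete data generated using multiple imputation".

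Two other sections fix what is observed. Data collection: "No additional data are to be collected if a participant discontinues study medication or in other ways does not comply with the intervention protocols". Interventions, on patients who withdraw or are withdrawn: "No further data will be collected from patients after leaving". The next sentence keeps what came before: "However, previously collected data will be part of the final data analysis".

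The Interventions section lists many routes out. On a pill count below 75% at week 2 or week 12: "If the patients do not comply with these demands at either visit, they will be excluded from the study". On a new coronary event: "Patients who have a recurrence of ACS during the study will be withdrawn from the study". On antidepressants: "Startup of any medical antidepressant treatment in the trial period is prohibited and will lead to exclusion from the trial". Withdrawn consent, pregnancy, cancer, a severe medical emergency or more than a week in hospital, and moderate or severe depression confirmed at interview also end participation.

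The primary outcome is an MDI score of 21 or more at any time after baseline, with the MDI completed every two weeks for 12 weeks.

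**The concern.** An intention-to-treat comparison asks what happens to patients as randomised, whether or not they keep taking the drug. Answering it from data needs outcomes after patients stop, and the collection rule prevents that. An analysis plan can choose a different imputation model, but it cannot recover scores that the protocol says will not be collected.

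A standard imputation model fitted to these data sees only scores recorded on treatment. It fills in a stopped melatonin patient much as if that patient were still taking melatonin. A mixed model on the observed scores extrapolates in the same way, and the log-rank and Cox analyses censor the same patients. All of these assume that leavers resemble those who stay, given what was recorded earlier. That is doubtful when the reason for leaving is an antidepressant start, a recurrent coronary event or poor adherence, since each may be related to mood.

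At stake is the meaning of the headline result. It would carry the intention-to-treat label but come closer to the effect had everyone stayed on treatment. If benefit is lost on stopping, that favours melatonin.

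**Working it through.** **1. The plan's own figure.** The Sample size section gives 31% v 15.5%, two-sided 5%, power 0.80. With the pooled-variance formula, mean risk 0.2325 and difference 0.155:

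n = [1.960·√(2·0.2325·0.7675) + 0.842·√(0.31·0.69 + 0.155·0.845)]² / 0.155² ≈ 115.4, rounded up to 116 per arm.

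The stated 116 reproduces, so the point concerns follow-up and not arithmetic. The target of 120 is only 4 per arm above it, and the reason given is block size.

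**2. Which outcomes are lost.**

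| Route out | Binary outcome (MDI ≥21 at any time) | Later scores in the mixed model |
|---|---|---|
| Confirmed moderate or severe depression | Normally already an event, since referral follows a moderate-to-severe MDI result | Lost |
| Antidepressant start | Kept if MDI had reached 21, otherwise unknown | Lost |
| Pill count below 75% at week 2 | Unknown for the remaining 10 weeks unless already an event | Lost |
| Pill count below 75% at week 12 | Little lost | Little lost |
| Recurrent ACS, emergency or long admission, cancer, pregnancy, stopping the drug | Unknown from exit unless already an event | Lost |

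**3. Size of the possible distortion.** The document gives no discontinuation rate, so a share d of 10, 20 or 30% of the melatonin arm is assumed to stop. Also assumed: the planned risks hold, imputation is done within arm from on-treatment data and so returns 31 − 15.5 = 15.5 points, and placebo patients who stop keep the 31% risk.

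*Upper bound: stoppers carry the full control risk from day 0.*
Difference = 0.31 − [(1 − d)·0.155 + d·0.31] = 0.155·(1 − d).

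*Stopping spread evenly over 12 weeks, constant hazards, control hazard after stopping.*
Cumulative hazards over 12 weeks are −ln 0.69 = 0.3711 (control) and −ln 0.845 = 0.1684 (melatonin). Averaged over stopping times, a stopper's event-free probability is (0.845 − 0.69)/(0.3711 − 0.1684) = 0.155/0.2026 = 0.765, so the risk is 23.5%.
Difference = 0.31 − [(1 − d)·0.155 + d·0.235].

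| Share stopping | All-randomised difference, upper bound | Overstated by | All-randomised difference, even stopping | Overstated by |
|---|---|---|---|---|
| 10% | 14.0 points | 11% | 14.7 points | 5% |
| 20% | 12.4 points | 25% | 13.9 points | 12% |
| 30% | 10.9 points | 43% | 13.1 points | 18% |

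Overstatement is 15.5 divided by the unrounded difference, minus 1; for example 15.5/12.4 − 1 = 25%.

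**The case against.** The strongest reply is that the analysis can be run as described. Everyone randomised can be entered, data from before exit are kept, recorded events stand, and the rest is imputed. A reader might infer that an intention-to-treat analysis is impossible, or that the result describes only patients who stayed on drug. The documents do not support either reading. What is lost is narrower: an effect regardless of adherence, estimated from observed outcomes.

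It can also be said that the imputation model and its sensitivity analyses belong in an analysis plan not shown here. That is fair, and their absence from the article is not the complaint. The article also plans to compare reasons for and timing of leaving between arms, which would reveal an imbalance in exits. It would not supply the missing scores.

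Two further inferences should be resisted. One is that leavers will be counted as free of depression. The Statistics section names multiple imputation and nowhere says this. The other is that safety follow-up stops at the most serious events. The sentence on collecting no further data is broad, but the article states GCP conduct and has a procedure for suspected unexpected serious adverse reactions. Adverse-event follow-up after withdrawal is commonly left to the full protocol.

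Finally, the 11, 25 and 43% figures treat stoppers as never having been treated. That objection stands, so they serve only as an upper bound beside the even-stopping figures.

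**Conclusion.** The concern holds in this limited form. The collection rule and the intention-to-treat promise do not fit together: for patients who leave before reaching MDI 21, and for every later score in the mixed model, the result depends on outcomes that by design are never seen. The trial's own data cannot check the assumption that replaces them.

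The size is illustrative. With 10 to 30% of the melatonin arm stopping, the overstatement is about 5 to 18% under even stopping and 11 to 43% at the upper bound. These figures rest on an assumed discontinuation rate, within-arm imputation, and loss of benefit after stopping. If benefit persists after stopping, the distortion shrinks. Because outcomes not collected cannot be recovered, this should be corrected while the trial is still enrolling.

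**What to change.** Amend the sentences in the Interventions and Data collection sections so that stopping medication, or meeting a withdrawal or exclusion criterion, ends study medication but not observation. Such participants are asked to keep completing the emailed two-weekly MDI to week 12. Only withdrawal of consent to data collection ends follow-up. The rules on when treatment stops stay as they are.

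Use the off-treatment scores in the intention-to-treat analysis and in the imputation model. Add one sensitivity analysis that imputes missing melatonin-arm scores from the placebo arm. This also covers patients who left before the amendment, whose later scores cannot be recovered.

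The cost is a short amendment, a check of the consent wording and extra reminders, since questionnaires already go out by emailed link. The gain is partial: with 150 of 240 included at publication, it helps the remaining 90 and those still in follow-up. An effect that includes off-treatment time may also be smaller than planned. In the upper-bound case, power with 120 per arm is 71.8, 60.5 or 48.6% at 10, 20 or 30% stopping, against 81.5% with none. That loss reflects the question the trial says it will answer and is no reason to leave it unobserved.

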### Statistics

Descriptive data on baseline characteristics and results will be presented as mean, SD, and *n* and presented in tabular form. Distribution of data will be tested by using data plots and by visually assessing data, and potentially continuous variables will be visualized in a matrix plot. Appropriate statistical tests will be used accordingly depending on distribution. Log transformation will be applied if applicable.

Our null hypothesis is that there will be no difference in the number of participants developing depressive symptoms (defined as a MDI score ≥21) throughout the study period between the melatonin and the placebo group. The hypothesis is assessed using Fisher’s exact test and/or the chi-squared test.

For the primary outcome analysis, a linear mixed model will be applied. The effect of age, gender, comorbidity and cardiac risk factors will be assessed by marginal analysis. Results will be assessed through an analysis on complete data generated using multiple imputation.

As a secondary analysis, the cumulative incidence of depressive symptoms will be plotted for the two groups and compared using the log-rank test assuming the absence of competing risks. Incidence of depressive symptoms (MDI score ≥21) will be analyzed using the Cox proportional hazards regression, including analysis of effects of age, gender, comorbidity and cardiac risk factors at baseline.

A principle analysis will be performed according to the intention-to-treat principle (ITT). The intention-to-treat population is defined as every patient randomized into the trial. A per-protocol analysis will also be performed. A per-protocol participant is defined as a patient who has taken medication in accordance with the protocol (at least 75%) for the first 14 days (until the follow-up visit). In cases of noncompliance with the medication before the follow-up visit (i.e., exclusion from the study), another patient will be enrolled to make up for the lost patient. Finally, a standard sensitivity analysis will be performed on the per-protocol patient population.

For secondary/exploratory outcomes, intergroup comparison for anxiety and depression (HADS) will be made at baseline, 2 and 12 weeks. The data originating from the actigraphy measurement will be presented as sleep and circadian outcomes. The sleep outcomes will be divided into units of 3 days as recommended [59], and descriptive data will be presented for the entire 2-week measuring period. Sleep diary and VAS measured each day simultaneously with actigraphy will be termed short-term sleep/VAS outcomes. Sleep diary and VAS measured afterwards every 2 weeks will be termed long-term sleep/VAS outcomes. Intergroup comparisons of PSQI data will be made at baseline, 4, 8 and 12 weeks. For all continuous data, intergroup comparisons will be done using an unpaired Student *t* test or Mann-Whitney’s test depending on distribution of data. For analysis of the correlation between circadian genotype, depressive symptoms and sleep, a logistic regression analysis will be used.

A *P* value < 0.05 will be considered statistically significant. For exploratory outcomes all analysis will be presented and no statistical correction for multiple testing will be applied [60]. No interim analysis is planned for the study. A priori, no subgroup analysis is planned [61]. The statistical analysis plan has been consulted with an external independent statistician. The analysis of data will, upon study completion, be handled and performed by the first author, and the process will be aided by the external study statistician. An appropriate statistical software package will be applied for the statistical analysis.

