### Primary outcome

The MDI is a self-rating scale with 12 questions. It has been extensively used in a Danish population [47] and is also thoroughly validated [48]. The questions cover the ten ICD-10 symptoms for depression, which are identical to the *Diagnostic and Statistical Manual of Mental Disorders, 4th edition* (DSM-IV) major depression diagnostic criteria except for one symptom, low self-esteem (question 4), which in DSM-IV is incorporated into a question about guilt (question 5).

The MDI holds a double function. It can be used as a diagnostic tool which, via an algorithm, can be transformed into the DSM-IV or ICD-10 categories of “mild,” “moderate,” or “severe” depression. The tool has been found to have satisfactory sensitivity and specificity with regard to the diagnosis of depression according to both the ICD-10 and DSM-IV [49]. The MDI can also be used as a rating scale, which can grade the severity of depression and this has been found to have an acceptable correlation with the Hamilton Depression Scale (HAM-D) [48].

For the purpose of the current study, the MDI will be used as a diagnostic tool at baseline with regard to the eligibility (inclusion/exclusion criteria) of the participants. Mild depression excludes participation and, as a diagnostic tool, mild depression is the presence of two core symptoms and two accompanying symptoms of depression. During the study, the MDI will be used as a rating scale to evaluate the severity and development of depressive symptoms. As a rating scale, a total MDI score (0–50 points) of 21 to 25 points corresponds to a mild depression, of 26 to 30 a moderate depression and above 31 points constitutes a severe depression. Incident depressive symptoms, defined as MDI score ≥21 any time after baseline MDI, is the primary outcome assessed using the MDI as a rating scale. Timing of outcome assessment can be seen in the SPIRIT figure (Fig. 3).

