### Sample size

Sample size is calculated on the basis of a conservative assumption that 31% of patients following ACS will develop depressive symptoms [4] which we assume can be reduced to 15.5% by melatonin treatment. Power calculation is based on two-sided test and, with a power of 0.80 and a significance level of 5% (*α* = 0.05), the required sample size in each group is 116. There are no interim efficacy analyses planned. The patients will be randomized in blocks of 6 and, therefore, the study will proceed until 120 patients have been enrolled in each arm.

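### The primary outcome, hypothesis and sample size are binary, but the primary analysis is given both as a linear mixed model and as Fisher and/or chi-squared, so no single deciding analysis is fixed

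*Protocol article*

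**What the plan says.** All references are to the protocol article.

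- **Primary outcome:** "Incident depressive symptoms, defined as MDI score ≥21 any time after baseline MDI, is the primary outcome". This is one yes/no value per patient.
- **Sample size:** the calculation assumes that "31% of patients following ACS will develop depressive symptoms", reduced to 15.5% on melatonin, with a two-sided test, 5% significance and 80% power. On that basis "the required sample size in each group is 116", and 120 per arm are to be enrolled.
- **Statistics, hypothesis:** the null concerns the number of participants who reach the cutoff. "The hypothesis is assessed using Fisher’s exact test and/or the chi-squared test".
- **Statistics, next paragraph:** "For the primary outcome analysis, a linear mixed model will be applied". The response variable, contrast and time point of that model are not named. Results are to come from multiply imputed data.
- **Statistics, ranking:** the time-to-event methods are clearly ranked: "As a secondary analysis, the cumulative incidence of depressive symptoms will be plotted for the two groups and compared using the log-rank test". The principal population is everyone randomised.
- **Statistics, multiplicity:** the threshold is P < 0.05, and the statement that no correction will be made is limited to exploratory outcomes.

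**The concern.** Three parts of the article agree on a comparison of two proportions. The sentence that assigns the primary outcome analysis then names a method for a continuous response, normally a repeated score. The two approaches have different effect measures and can give different answers. The article ranks log-rank and Cox as secondary, yet leaves both the binary test and the mixed model in the primary position, with no rule for a split result.

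Within the binary comparison, the text also leaves open which of two tests is used. They can fall on opposite sides of 0.05, and the sample size matches only one of them.

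At stake is whether a borderline or split result could be read as confirmatory. The stated power belongs to one of the named options only, and the 5% error rate is not protected if more than one result may be claimed.

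**Working it through.** **Inputs from the article:** 31% v 15.5%, two-sided 5%, power 80%, 1:1 allocation, 116 per arm calculated and 120 enrolled.

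**1. Reproducing 116.** For two proportions, pooled variance under the null and no continuity correction:

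n = [1.95996 × √(2p̄(1 − p̄)) + 0.84162 × √(p₁(1 − p₁) + p₂(1 − p₂))]² / (p₁ − p₂)²

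- p̄ = (0.31 + 0.155)/2 = 0.2325, and √(2 × 0.2325 × 0.7675) = √0.35689 = 0.59740
- √(0.31 × 0.69 + 0.155 × 0.845) = √0.34488 = 0.58726
- Numerator: (1.17088 + 0.49425)² = 2.7727. Denominator: 0.155² = 0.024025
- n = 115.4, so 116 per arm, which matches the article.

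The alternatives do not give 116: unpooled variance 113, arcsine 114, continuity-corrected 128. The stated figure is therefore that of the uncorrected chi-squared test.

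**2. Exact power at 31% v 15.5%**, by enumerating every 2×2 table:

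| Per arm | Uncorrected chi-squared | Fisher's exact |
|---|---|---|
| 116 | 80.6% | 76.4% |
| 120 | 82.1% | 77.9% |

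Fisher's test is at 79.95% with 126 per arm and first reaches 80% at 127 (80.4%).

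**3. Can the two binary tests disagree?** Yes, in one direction. At 120 per arm and the planned effect, about 4.3% of trials have chi-squared P < 0.05 and Fisher P ≥ 0.05. Example: 37/120 v 23/120. The pooled proportion is 60/240 = 0.25 and the difference is 14/120 = 0.1167. The standard error is √(0.25 × 0.75 × 2/120) = 0.0559, so z = 2.087 and chi-squared P = 0.037. Fisher's P is 0.052.

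**4. Does that choice inflate the type I error?** No. With a common rate of 15.5%, 23.25% or 31%, and 116 or 120 per arm, Fisher rejects in 3.2% to 3.6% of trials and chi-squared in 4.95% to 5.1%. Taking the better of the two also gives 4.95% to 5.1%, because Fisher was never significant where chi-squared was not.

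**5. Adding the mixed model.** The article gives no score distribution, so these inputs are assumptions. The null simulation used 120 per arm, six post-baseline visits, normal scores with exchangeable correlation, 31% ever above the cutoff, no dropout, and 40,000 trials per setting. With such balanced data the model's group effect reduces to a t test on patient means.

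| Correlation | Chi-squared or group effect | Chi-squared or group-by-time slope | Any of the three |
|---|---|---|---|
| 0.3 | 8.7% | 9.7% | 13.2% |
| 0.5 | 8.3% | 9.8% | 13.0% |
| 0.7 | 8.2% | 9.7% | 12.9% |

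A second simulation used log-normal scores, baseline below 21, intraclass correlation 0.5 to 0.7, 17% to 20% events and 4,000 trials per scenario. It gave 8.2% to 9.4% for chi-squared or the mixed model. For reference, two independent tests give 1 − 0.95² = 9.75%.

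**6. Power if the mixed model decides.** This cannot be computed, because the article states no mean difference, standard deviation or within-patient correlation.

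**The case against.** The best defence is that the Statistics section says the hypothesis is assessed by the binary test. That test can then be read as decisive, with the mixed model as supporting estimation or covariate adjustment. On that reading the type I error is about 5%. The choice between Fisher and chi-squared is also a detail often left to an analysis plan, and here it costs about two points of power against the 80% target at 120 per arm. This second part stands: alone, the and/or wording would be a minor remark. The first part is a possible reading, but the next paragraph gives the mixed model the primary label, and a conflict between two statements is not an omission that a later plan simply fills in.

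Three stronger readings are tempting and are not supported:

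- *Neither the error rate nor the stated power holds.* The stated power does hold for uncorrected chi-squared, a test the article names. If any test may win, power is at least that of chi-squared. No single reading makes both fail.
- *Leaving Fisher or chi-squared open inflates the error rate.* Step 4 shows that it does not.
- *The plan lets the sponsor claim whichever result is significant.* The article has no such rule. It lacks a rule that prevents it, so the 8% to 10% is conditional.

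It is also an inference, though a natural one, that the mixed model would compare mean MDI scores, since its response is not named.

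**Conclusion.** The point holds as an internal contradiction: a binary outcome, hypothesis and sample size sit beside a primary analysis by linear mixed model and an unresolved pair of binary tests. It should be settled before unblinding.

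The consequence depends on which analysis decides. Under uncorrected chi-squared, the planned size and error rate stand. Under Fisher, power falls below 80% at both 116 and 120 per arm. Under the mixed model, power has no stated basis. The error rate is exceeded only if the binary test and the mixed model may each count as success. It is then roughly 8% to 10%, or about 13% if two model contrasts are open.

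The binary-test figures are exact, given the article's rates and complete data. The mixed-model figures rest on assumed distributions, correlations and visit numbers, although two simulations with different distributions agree closely.

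**What to change.** Before unblinding, amend the Statistics section and align the analysis plan:

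1. Name one primary analysis: the difference in the proportion with MDI of 21 or more by week 12, in the intention-to-treat population.
2. Fix its form. If the planned multiple imputation is kept, the deciding result is the risk difference pooled by Rubin's rules, with events derived from the imputed MDI scores. If it is not, the deciding result is the uncorrected chi-squared test used for the sample size. State which applies, so that no second choice stays open.
3. Delete Fisher's exact test and the and/or. If the sponsor prefers Fisher, restate the power as about 78% at 120 per arm.
4. Relabel the linear mixed model of MDI scores as a secondary analysis.

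The cost is protocol and analysis-plan wording, with no new data and no extra patients unless Fisher is kept and 80% power is still wanted (127 per arm). The article reports 150 of 240 patients included and describes the data analysts as blinded, so at that point the change could be made without knowledge of results by arm. The downside for the sponsor is that success could no longer be claimed on the mixed model alone.
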